| Technical Summary (Max. 300 words) Recent investigations and meta-analyses indicate a strong association between bilirubin and renal outcomes. We wish to conduct a retrospective study on CPRD GOLD dataset to investigate these associations in a real-world setting. Based on our preliminary feasibility count, we believe the cohorts retrospectively built using CPRD GOLD dataset will be at least one order of magnitude larger than the analyses that are currently available. Also, we should be able to adjust critical confounders such as haemoglobin level and smoking status that was previously not done or lead to inconclusive results.  We will retrospectively build two cohorts with known risk factors for CKD: type 2 diabetes or hypertension. We will follow the patients from the date of diagnosis of either of these morbidities to one of the events indicating the degradation of renal function (eGFR decrease, serum creatinine increase, albuminuria, or proteinuria). We will fit the Cox proportional hazard models with inverse probability weighting to estimate the adjusted hazard ratio between the patients with elevated bilirubin vs. normal levels.  We are aware that as this will only be the observational study and we will not be able to conclude the causality of bilirubin levels to CKD progression even if we can show an association. However, with careful analyses based on richer dataset than what is currently available, this analysis may increase our understanding of the association between bilirubin and CKD outcomes and guide further investigations. |
| Outcomes to be Measured  1. Time to eGFR CKDEPI 30% decrease from the baseline; 2. Time to first observation of proteinuria; 3. Time to first observation of albuminuria. |

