| Objectives, Specific Aims and Rationale Overall Primary Objective:  1a) To investigate the risk of worsening of renal function using eGFR (using CKD EPI formula) in relation to bilirubin levels in type2 diabetic patients, in a real-world setting.  1b) To investigate the risk of worsening of renal function using eGFR in relation to bilirubin levels in hypertensive patients, in a real-world setting.  Secondary objectives:  2a) To investigate the risk of worsening of renal function using urine albumin creatinine ratio (UACR) in relation to bilirubin levels in type2 diabetic patients, in a real-world setting.  2b) To investigate the risk of worsening of renal function using UACR in relation to bilirubin levels in hypertensive patients, in a real-world setting.  Exploratory objectives:  3a) To investigate the risk of worsening of renal function using amount of protein in urine in relation to bilirubin levels in type2 diabetic patients, in a real-world setting.  3b) To investigate the risk of worsening of renal function using amount of protein in urine in relation to bilirubin levels in hypertensive patients, in a real-world setting.  Specific aims:   \| **Primary objectives**  1a) To investigate the risk of worsening of renal function using eGFR in relation to bilirubin levels in type2 diabetic patients, in a real-world setting.  1b) To investigate the risk of worsening of renal function using eGFR in relation to bilirubin levels in hypertensive patients, in a real-world setting. \| **Outcome measure**  Time to first of first two consecutive measurements of eGFR that are 30 percent less than the eGFR at baseline. \| **Hypothesis tested**  1a) Naturally elevated serum bilirubin level of type2 diabetic patients is associated with slower degradation of the renal function when renal function is measured using eGFR.  1b) Naturally elevated serum bilirubin level of hypertensive patients is associated with slower degradation of the renal function when renal function is measured using eGFR. \| \| --- \| --- \| --- \| \| **Secondary objective**  2a) To investigate the risk of worsening of renal function using urine UACR in relation to bilirubin levels in type2 diabetic patients, in a real-world setting.  2b) To investigate the risk of worsening of renal function using UACR in relation to bilirubin levels in hypertensive patients, in a real-world setting. \| **Outcome measure**  Time to first observation of albuminuria (UACR >30mg/g) during the follow up period. \| **Hypothesis tested**  2a) Naturally elevated serum bilirubin level of type2 diabetic patients is associated with slower degradation of the renal function when renal function evaluated by UACR.  2b) Naturally elevated serum bilirubin level of hypertensive patients is associated with slower degradation of the renal function when renal function evaluated by UACR. \| \| **Exploratory objective**  3a) To investigate the risk of worsening of renal function using amount of protein in urine in relation to bilirubin levels in type2 diabetic patients, in a real-world setting.  3b) To investigate the risk of worsening of renal function using amount of protein in urine in relation to bilirubin levels in hypertensive patients, in a real-world setting. \| **Outcome measure**  Time to first observation of proteinuria during the follow up period. \| **Hypothesis tested**  3a) Naturally elevated serum bilirubin level of type2 diabetic patients is associated with slower degradation of the renal function when renal function evaluated by proteinuria.  3b) Naturally elevated serum bilirubin level of hypertensive patients is associated with slower degradation of the renal function when renal function evaluated by proteinuria. \|   **Rational:**  Recent investigations as well as meta-analyses indicate a strong association between serum bilirubin concentrations and renal outcomes. This association has led us to hypothesis that elevated bilirubin level is associated with slower degradation of kidney function. There are still discussions on this association because the previous investigations lack diversity in the patient population and did not adjust for the key confounders. We wish to conduct a retrospective study in a real-world setting to support or dispute this hypothesis. This study will provide the medical community extra piece of evidence for or against the bilirubin as a potential predictive marker for CKD progression as well as the target for preventative treatment option. |

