| Feasibility counts The number of patients in each cohort and number of patients who will be included in the analysis of each objective is listed below (the feasibility count is conducted using the CPRD data up to July 2018) please see Appendices 1 and 2 for exclusion diagram, please see Section L for inclusion exclusion criteria as well as objective specific exclusion criteria:   \|  \| CH1 (Type2 Diabetic patients) \| CH2 (Hypertensive patients) \| \| --- \| --- \| --- \| \| Number of subjects in Cohort \| 68 217 \| 85 409 \| \| Number of subjects for the analyses of the primary objectives 1a) and 1b) (endpoint: eGFR 30% decrease) \| 66 509 \| 81 025 \| \| Number of subjects for the analyses of the exploratory objectives 3a) and 3b) (endpoint: albuminuria) \| 45 168 \| 79 975 \| \| Number of subjects for the analyses of the secondary objectives 2a) and 2b) (endpoint: proteinuria) \| 66 317 \| 84 335 \| |
| Sample size considerations Based on our analyses on in-house randomised control clinical trial (RCT) data of type2 diabetic patients, we guess the hazard ratio for the primary endpoint to be 0.8 for the above median bilirubin level subgroup, in addition, we assume 5% type I error is tolerable and require 80% power. Based on these assumptions, using the formula derived by Schoenfeld (8), using the implementation available at <http://www.sample-size.net/sample-size-survival-analysis/>, we obtain that we need 631 events.  Using internal AZ data from a recent RCT we calculated our sample size estimate. In that in-house dataset, the event rate was approximately 0.047 per year per person. Hence assuming similar event rates, we require 13 500 person-year to achieve this power. According to our feasibility count, each cohort will include over 60 000 patients with a median follow up period of approximately 5 years (i.e., most likely over 300 000 person-year), hence we believe we have enough power to reliably conduct this study. |
| Planned use of linked data (if applicable): We will not use linked data. |

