| Definition of the Study population This study will examine two patient cohorts who are at risk of CKD, diabetic and hypertensive patients. Eligible patients must have information recorded at least 12 months prior to the study index date and have up to standard (UTS). The study population will include patient records from January 2005 to January 2019.  **Inclusion criteria**  Cohort 1 (CH1) will include type 2 diabetes mellitus (T2D) patients along with any one of the following criteria (see Appendix 1 for the inclusion exclusion flow chart):   - Newly diagnosed T2D (MEDCODE 758 : Type 2 diabetes mellitus) - 2 prescriptions of diabetic medication (See Appendix 3 for the list of all drugs) - Hemoglobin A1c (HbA1c) value greater than 6.5   Cohort 2 (CH2) will include essential hypertension (EHT) patients along with the following criteria (see Appendix 2 for the inclusion exclusion flow chart):   - Newly diagnosed essential hypertension (see Appendix 4 for list of Read codes)   Time related variable including the index date and the follow-up is described in the following figure:  **Rolling index date**  (The date first diagnosed with DM2 or HT**)**  Pre-index period  1 years  Acute disease period  2 years  Follow up period  (Median follow up 5 years, minimum follow up 1 year)  **End of follow up**  (Either the date patient has transferred out from the practice  Or the last date of the record in the dataset)  **CH1**: no DM2 diagnosis nor related medication during this period **CH2**: no HT diagnosis nor DM2 diagnosis nor related medication during this period  Baseline is characterized based on the observation in these periods  January 2005  January 2019  **Exclusion criteria**  We will exclude the following patients based on the Read code during acute disease period (2 years after the rolling index date):   - Liver dysfunction including drug induced liver injury (diagnosis with Read code listed in Appendix 5 and/or Aspartate transaminase (AST) and alanine transaminase (ALT) levels outside of the normal range (AST: 8-48U/L, ALT: 7-55U/L) - Anemia (hemoglobin level below cutoff, female:120 male:130 g/L, or with the clinical annotation of primary or secondary anemia with the Read code listed in Appendix 6) - Human immunodeficiency virus (HIV) infection and or on HIV related medications (see Appendix 7). - All malignancies and or on medications related to the treatment for the malignancies (see Appendix 8). - Age < 40 (to exclude type 1 diabetic patients). - Any user of UGT1a1 inhibitors (see Appendix 9) during the acute disease period. - < 1 year of clinical records in the database before the index date - Pregnant women - Patients with clinical record of alcohol dependencies. - Any patients with less than two bilirubin measurements during the acute disease period.   **Objective-specific exclusion criteria**  For each endpoint, we impose the following additional exclusion criterion:   - For objectives 1a) and 1b) with the endpoint “First two consecutive measurements of eGFR that are 30 percent less than the last eGFR record during the acute disease period”, we will exclude patients without eGFR records during the acute disease period (2 years after the rolling index date). - For objectives 2a) and 2b) with the endpoint “First observation of albuminuria (UACR >30mg/g) during the follow up period.”, we will exclude patients with recorded UACR more than 30mg/g during the acute disease period. - For objectives 3a) and 3b) with the endpoint “First observation of proteinuria during the follow up period, we will exclude the patients with the recorded proteinuria (protein dipstick test result +, ++, or +++) during the acute disease period. |

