| Selection of comparison group(s) or controls We will stratify the patients based on the population median of the patient mean baseline serum bilirubin levels from the tests table under ENTTYPE 158. We consider the patients with less than or equal to the median serum bilirubin level to be the control group, and patients with greater than the median serum bilirubin level to be the exposure group.  The serum bilirubin levels are determined by the average of all the available measurements during the acute disease period (2 years after the rolling index date). We require at least two bilirubin measurements to be used to obtain an average estimate (this will account for the variability of bilirubin measurements). |
| Exposures, Outcomes and Covariates **Outcome:**  Outcomes will include the following events:  Primary objective: eGFR decline  1) First two consecutive measurements of eGFR that are 30 percent less than the last eGFR record during the acute disease period.  eGFR will be calculated using CKD EPI formula based on the recorded serum creatinine measurements in tests table ENTTYPE 165.  Secondary objective: Proteinuria  2) First observation of the proteinuria  Proteinuria is defined as the protein dipstick test results either +, ++ or +++, recorded in the tests table under ENTTYPE 431.  Exploratory objective: Albuminuria  3) First observation of the albuminuria  Albuminuria is defined as the recorded UACR measure in test table under ENTTYPE 469 greater than 30mg/g.  **Covariates:**  We will use all the available covariates (see Appendix 10) to calculate the propensity score that we will use for the inverse probability weighting of the Cox proportional hazard model.  We will include all the available covariates (see Appendix 10) in the baseline table.  We will include the following selected covariates in the multivariate Cox proportional hazard model:   - Age, Sex, Weight, BMI, Baseline eGFR, Baseline UACR, Baseline protein dipstick result, Smoking status, Serum Haemoglobin level, HDL cholesterol, LDL cholesterol - Use of the following drugs: ACE inhibitor, Statin, Diuretics, Opioids, Potassium-sparing diuretics |

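### The primary eGFR event needs two consecutive low values but sets no minimum interval between them, so one short episode tested twice can count as decline; a post hoc spaced-confirmation sensitivity analysis should be added

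*Protocol*

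**What the plan says.** The protocol describes the primary eGFR event in four places.

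- *Exposures, Outcomes and Covariates* and the objective-specific exclusions under *Definition of the Study population*: "First two consecutive measurements of eGFR that are 30 percent less than the last eGFR record during the acute disease period".
- *Objectives, Specific Aims and Rationale*, table of specific aims: "Time to first of first two consecutive measurements of eGFR that are 30 percent less than the eGFR at baseline". This also fixes the event date at the first of the two values.
- *Outcomes to be Measured*: "Time to eGFR CKDEPI 30% decrease from the baseline". A second value is not mentioned.

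The values come from routine records: "eGFR will be calculated using CKD EPI formula based on the recorded serum creatinine measurements in tests table ENTTYPE 165". The rationale presents the study as evidence on "bilirubin as a potential predictive marker for CKD progression".

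**The concern.** A second low value is normally required to show that a fall has persisted. With no minimum interval, it shows only that eGFR was low on two tests in a row. Those tests may be days apart in a single illness from which kidney function recovers. Such an event is dated and counted like a lasting loss of function.

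The hypothesis is about the pace of kidney function loss. Events from a different, reversible process would pull the hazard ratio towards 1 if they are unrelated to bilirubin. If acute illness is related to bilirubin, they could distort it in a direction that the documents do not allow one to predict. The definition also makes an event depend on how soon a patient with a low value is retested.

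**Working it through.** **1. Does anything else in the protocol close the gap?**

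- *Visit schedule.* None exists. Creatinine is taken from the primary care tests table as recorded, so spacing is whatever practice produced.
- *Exclusions.* The list does not name acute kidney injury. It mostly concerns the two-year acute disease period, whereas the events occur in the follow-up after it. The exclusion specific to this endpoint only requires an eGFR record in that period.
- *Linkage.* "We will not use linked data", so linked hospital records cannot be used to identify acute episodes.
- *Sensitivity analyses.* Under *Data/ Statistical Analysis* these vary the weighting, the bilirubin cut-off, the subgroup and the availability of bilirubin measurements. None varies the event definition.
- *Mixed effect model on eGFR.* This is an additional analysis and does not change the primary event or its hazard ratio.

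So two low values days apart, followed by full recovery, are an event as the protocol is written.

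**2. Reproducing the plan's figures.** Inputs from *Sample size considerations*: hazard ratio 0.8 ("we guess the hazard ratio for the primary endpoint to be 0.8 for the above median bilirubin level subgroup"), 5% type I error (taken as two-sided), 80% power. The median split gives allocation of about 1:1.

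- Schoenfeld: events = (1.960 + 0.842)² / (0.25 × ln(HR)²) = 7.849 / (0.25 × ln(0.8)²) = 630.5, rounded up to 631. This matches the plan.
- Person-years: 631 / 0.047 = 13,426, consistent with the stated 13 500.
- Events expected per cohort: 0.047 × 300,000 = 14,100.

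**3. Possible size of the dilution.** The transient share is not in the documents, so it is an assumption shown over a range. Let a fraction f of control-group events be transient and equally frequent in both groups (hazard ratio 1), with 0.80 for the rest. Then observed HR = (1 − f) × 0.80 + f.

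| f (assumed) | Observed HR | Events for 80% power |
| --- | --- | --- |
| 0% | 0.80 | 631 |
| 10% | 0.9 × 0.80 + 0.1 = 0.82 | 798 |
| 20% | 0.8 × 0.80 + 0.2 = 0.84 | 1,033 |
| 30% | 0.7 × 0.80 + 0.3 = 0.86 | 1,381 |

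**4. Does power matter?** No. Even the 1,381 events of the last row would need a rate of only 1,381 / 300,000 = 0.0046 per person-year, about a tenth of the 0.047 assumed. With the stated 66 509 and 81 025 patients, five years each and 0.047 per person-year, about 15,600 and 19,000 events are expected, and power exceeds 99.9% in every row.

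**The case against.** **The protocol already requires confirmation.** This stands in part. An isolated low value followed by recovery is not an event, and an acute episode counts only if it is tested at least twice in a row while eGFR is low. It does not remove the case of prompt retesting.

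**Frequent retesting within days is not documented.** This stands. No section gives retesting intervals, and the data are general practice tests without hospital linkage, so dense inpatient testing cannot be assumed to appear. The 10% to 30% range is illustrative.

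**Spacing is a derivation rule for the analysis plan.** The analysis plan is not at hand and may contain such a rule. But the protocol sets out the event in full in three places, in a form that can be applied as it stands, and in a fourth place gives a version without confirmation.

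**The wording points are small.** This stands. The outcomes list is a summary, and few would read 30 percent less as exactly 30 percent. Both are tidying.

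**A 90-day rule has faults of its own.** This stands. If the event is dated at the first value but needs a later one, event status depends on the patient surviving, staying registered and being tested again. Someone who dies or transfers out soon after a real decline loses the event.

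**The 0.8 may already include transient events.** This is possible. It was guessed from in-house trial data whose event definition is not given. The table therefore shows the direction and order of the shift, not a prediction.

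**Conclusion.** The gap is real and of modest weight. The protocol's primary event accepts two low values at any spacing, and nothing else in the document limits this. Under the assumption of transient events unrelated to bilirubin, at 10% to 30% of control-group events, a hazard ratio of 0.80 would appear as 0.82 to 0.86. The consequence is for the size and interpretation of the estimate.

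Three stronger conclusions might be inferred, and the documents support none of them.

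- *The study is underpowered.* The rising event counts have no practical effect against about 14,100 expected events.
- *The primary definition should be replaced.* The amendment of 12 February 2021 reports primary hazard ratios of 0.88 (diabetic cohort) and 0.91 (hypertensive cohort). Changing the primary event now would be a post hoc change made with the results in view.
- *Transient events explain why those two hazard ratios are so close.* Different transient shares in the two cohorts could in principle have that effect, but nothing in the documents shows the shares or that they differ.

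**What to change.** 1. Keep the planned two-value event as primary. Word the threshold as at least 30 percent below baseline, and bring *Outcomes to be Measured* into line with the full definition.
2. Add to the sensitivity analyses, labelled post hoc, a version in which the confirming value falls at least 90 days after the first, with no intervening value above the threshold. Keep the first value as the event date and report the hazard ratio beside the primary one. The 90 days is this review's proposal, not a figure from the documents.
3. Report, by exposure group, how many patients have a first low value that cannot be confirmed because of death, transfer or no later test. An imbalance there would limit what the sensitivity analysis can show.

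The cost is one extra endpoint derivation from data already held, and fewer events in that analysis. Losing half would still leave 14,100 / 2 = 7,050, about five times the 1,381 in the most diluted row above. The dependence on later survival, registration and testing remains, and is why this belongs beside the primary analysis rather than in its place.

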| Data/ Statistical Analysis Baseline characterization  The baseline characteristics will be described by the exposure groups (high and low bilirubin level at baseline). Summary statistics such as counts, average, standard deviation, median, and inter-quantile range will be tabulated.  Formal analysis of individual cohort  Multivariate Cox’s proportional hazard model with stabilized inverse probability weighting scheme (9,10) will be used to calculate the Hazard ratios (HR) with 95% confidence interval for the outcomes (worsening of eGFR, proteinuria, and albuminuria).  Sensitivity analysis  We will test the robustness of the results from the formal analysis by testing the sensitivity to   - the use of inverse probability weighting. (We will repeat the formal analysis without inverse probability weighting and compare the HR) - the cut-off value for the serum bilirubin level for dividing control and exposure group. (We will repeat the formal analysis with different bilirubin cut-offs and compare the HR) - the subpopulation of the patients. Subgroups will be made based on the following covariates: Age, Sex, smoking status, Baseline eGFR, Baseline UACR, Baseline protein dipstick result, Use of ACE inhibitor, Statin, Diuretics, Opioids, Potassium-sparing diuretics. (We will conduct subgroup analysis with test of interaction between the subgroup and exposure-control groups)   In addition, to investigate the possible bias introduced by the fact we are including only the patients with two or more bilirubin measurements at the baseline, we will repeat the above analyses but compare the patient population with baseline bilirubin measurement v.s. no baseline bilirubin measurements.  Additional analysis   - We will characterize bilirubin as continuous variable to understand the medically important nonlinear relationship between bilirubin concentration and outcomes. - We will build mixed effect model on eGFR and test statistical significance of bilirubin level as a covariate using likelihood ratio test to better understand the time course variation of eGFR in relation to bilirubin level. |
| Plan for addressing confounding We will use inverse-probability weighting to address the confounding. |
| Plans for addressing missing data We will use missing indicator method to handle missing data. |

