| Patient or user group involvement (if applicable) No patient/user groups will be engaged in any way.  This is an explorative study to better understand the impact of bilirubin on a population level. Furthermore, no patients will be contacted we will only use CPRD retrospective data and we do not have any plans to assess quality of life. This is an exploratory study which will further our scientific knowledge about the impact of bilirubin on renal outcomes and potentially support the design of future clinical trials. |
| Plans for disseminating and communicating study results, including the presence or absence of any restrictions on the extent and timing of publication We plan to communicate the study result regardless of either positive or negative result though academic publication in a medical journal. As this is an academic project for the postdoctoral research fellow (YA) and he is hired for this project with time limiting contract (ending September 2020, extendable up to September 2021) hence the manuscript needs to be submitted to the journal before the end of his contract.  **Conflict of interest statement:**  All the investigators are employed by AstraZeneca, however, this study does not focus on AstraZeneca or any other medicines. |
| Limitations of the study design, data sources, and analytic methods As bilirubin is endogenous substance, the patients are exposed to them throughout their entire life hence the development of type 2 diabetes or hypertension can be affected by bilirubin.  Also, it is known that the natural level of bilirubin depends on the race, gender and other patient characteristics. Hence there will be a bias in baseline characteristics for exposure groups. Furthermore, as our primary analysis compares bilirubin levels it is only possible to conduct these analyses among subjects with bilirubin measurements and baseline measurements of each outcome. This may impact generalizability of the results. Sensitivity analyses will be conducted to address this limitation.  CPRD is a UK database limiting generalizability to other countries. In addition, it may not be possible to rule out the impact of unmeasured confounding factors on the primary/secondary objectives although we will adjust for all the measured confounding factors through the inverse probability weighting. |

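### The check on the two-test rule compares tested with untested patients, so it never re-estimates the bilirubin hazard ratio and cannot show whether that ratio is biased

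*Protocol*

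**What the plan says.** The protocol's exclusion criteria (Definition of the Study population) remove "Any patients with less than two bilirubin measurements during the acute disease period", that is, in the two years after the index date. Among those who remain, Selection of comparison group(s) or controls splits on the median of the patient means: "patients with greater than the median serum bilirubin level to be the exposure group", and "patients with less than or equal to the median serum bilirubin level to be the control group". The formal analysis is a stabilised inverse-probability-weighted multivariate Cox model for that contrast.

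Data/ Statistical Analysis then lists three sensitivity checks: dropping the weights ("We will repeat the formal analysis without inverse probability weighting and compare the HR"), changing the bilirubin cut-off, and subgroups. It adds a fourth, whose purpose is "to investigate the possible bias introduced by the fact we are including only the patients with two or more bilirubin measurements at the baseline" and whose method is "we will repeat the above analyses but compare the patient population with baseline bilirubin measurement v.s. no baseline bilirubin measurements".

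The Limitations section notes that the analysis is possible only in patients with bilirubin and baseline outcome measurements, and continues: "This may impact generalizability of the results. Sensitivity analyses will be conducted to address this limitation".

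**The concern.** The stated aim and the stated method do not match. The bias in question concerns one quantity: the hazard ratio for high versus low bilirubin, estimated only in patients with two or more tests. To learn whether the restriction distorts it, that same ratio has to be estimated again under a weaker or corrected restriction. The planned check instead makes being tested the exposure, and no bilirubin effect remains in the model.

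The other three checks all stay inside the tested population, so this is the only one written to address selection by testing. The February 2021 amendment reports primary hazard ratios of 0.88 (diabetic cohort) and 0.91 (hypertensive cohort). With effects this close to 1, a reader will want to know whether selection could matter. This check could be taken as reassurance or as a warning when it supports neither.

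**Working it through.** **The plan's own figures.** The protocol gives no number for this check. Its one design figure reproduces: with hazard ratio 0.8, two-sided 5%, 80% power and a 1:1 split, events = 4(1.960 + 0.842)² / (ln 0.8)² = 631, as stated. Then 631 / 0.047 = 13,426 person-years, against about 13,500 stated. The point below does not depend on it.

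**Aim against method.**

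| | Formal analysis | Planned check |
|---|---|---|
| Population | Two or more tests | Tested plus untested |
| Exposure | Mean bilirubin above the median or not | Any test or none |
| Ratio estimated | High versus low bilirubin | Tested versus untested |
| Other cut-offs | Possible | Not possible: no value in the untested |
| Exactly one test | Excluded | Has a measurement, but fails the two-test rule: not placed |

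**Can the two ratios move apart?** This was examined by simulation. The testing mechanisms and risk-factor effects are assumptions, not figures from the protocol.

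*Model 1.* 1.5 million patients, base rate 0.047 per year (from the protocol), 5 years of follow-up. High bilirubin in 50%. A risk factor U in 50%, with hazard ratio 2, left out of the Cox models.

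| Testing mechanism | Bilirubin HR, everyone | Bilirubin HR, tested only | Tested vs untested HR |
|---|---|---|---|
| Depends on U only (75% vs 25%) | 0.81 | 0.81 | 1.40 |
| Depends on bilirubin and U jointly (20%/80%), no true effect | 1.00 | 0.67 | 1.00 |
| Same pattern (30%/70%) | 0.81 | 0.61 | 1.02 |
| At random | 0.80 | 0.80 | 1.00 |

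*Model 2.* 600,000 patients, u standard normal, x = high bilirubin, logit P(tested) = −0.3 + a·u + b·x·u, hazard = 0.03·exp(0.5u + ln(0.9)·x), 5 years. Ranges are over repeated runs.

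| a, b | Bilirubin HR, everyone | Tested only, u ignored | Tested vs untested, u ignored |
|---|---|---|---|
| 0.8, 0 | 0.90 to 0.91 | 0.90 | 1.39 to 1.43 |
| 0.4, −0.8 | 0.91 | 0.72 to 0.74 | 1.01 to 1.03 |
| 0.25, −0.5 | 0.90 | 0.78 to 0.79 | 1.00 to 1.01 |

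In the first row of each model the check signals a difference although the bilirubin ratio is unbiased. In the two joint-selection rows of each model it is close to null although the tested-only ratio is well off.

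**What happens if u is measured.** The plan says the analyses are repeated, so covariates and weights apply. With u in the models:

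- Row 1 of Model 2: the tested-versus-untested ratio falls from about 1.40 to 0.99 to 1.00.
- Rows 2 and 3: the tested-only bilirubin ratio returns to 0.90 to 0.91 and 0.90 under the exposure weights already planned.

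So the discordance arises only when the factor driving testing is unmeasured.

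**Would selection weighting help?** In row 2 of Model 2, weighting by the inverse probability of being tested given u changes nothing (0.737 with and without). Selection there depends on bilirubin, which untested patients lack. In a variant where a measured factor both drives testing and modifies the bilirubin effect, it does help: tested-only 1.15, selection-weighted 1.05, full cohort 1.04.

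**The case against.** Three replies carry weight.

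First, crude simulated ratios do not represent the planned analysis, which weights on all the Appendix 10 covariates and adjusts for a selected set. That is right. Once the driving factor is measured, both the false alarm and the bias disappear. The joint-selection cases also use patterns chosen so that the contrast is near null: in Model 2 the slope of testing on u is +0.4 in low-bilirubin and −0.4 in high-bilirubin patients (or ±0.25). Nothing in the protocol supports such a pattern. A reader might infer from these figures that the study's hazard ratio is biased by the two-test rule, or take 0.73 against 0.90 as a measure of by how much. The documents support neither. The simulations show only that the check cannot tell the cases apart. Unmeasured selection is where a check is most needed, and there it fails.

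Second, the comparison does bear on generalizability. This also stands: whether tested and untested patients differ in adjusted renal risk is useful to know, and the comparison should be kept. A reader might go further and say that the Limitations section rests its case against bias on this one check. It does not. It speaks of generalizability, also covers missing baseline outcome measurements, and promises sensitivity analyses in general without naming this contrast. The claim about bias is made only in Data/ Statistical Analysis.

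Third, this is one supplementary analysis in a study that calls itself exploratory, and neither the primary estimate nor the sample size depends on it. That limits the stakes but does not repair the mismatch. Nor can it be left to a later analysis plan as missing detail, because the protocol states the contrast explicitly.

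**Conclusion.** Wrong as written. The protocol states an aim about bias from the two-test rule and fixes an analysis that cannot meet it. The contrast contains no bilirubin effect, cannot be repeated at other cut-offs, and leaves one-test patients unplaced. Neither a null nor a non-null result identifies bias in the bilirubin hazard ratio. It informs only whether tested and untested patients differ in renal risk.

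The logical point rests on the protocol's wording alone and needs no assumption. The simulated size (tested-versus-untested about 1.4 with no bias; about 1.0 with a tested-only ratio of 0.73 to 0.79 against 0.90) rests on assumed testing mechanisms with the driving factor unmeasured. It says nothing about whether the reported 0.88 and 0.91 are biased.

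**What to change.** 1. Re-estimate the high-versus-low bilirubin hazard ratio, using the formal analysis, in patients with at least one bilirubin measurement in the acute disease period. This relaxes the two-test rule directly and places the one-test patients. The downside is a noisier exposure than an average of two or more measurements.
2. As a further check, re-estimate it with the exposure weight multiplied by a stabilised inverse-probability weight for having two or more tests. Model that probability on the Appendix 10 covariates in the cohort before the bilirubin exclusion. State that this carries the ratio to the full cohort when measured factors drive testing and modify the effect, and that it does not correct selection that depends on bilirubin itself or on unmeasured factors.
3. Keep the adjusted tested-versus-untested comparison, but label it as describing representativeness and not as a test of bias in the bilirubin hazard ratio. State in which group one-test patients fall.

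The cost is one additional weight model, two reruns and a change of wording. The planned contrast already needs the data on patients outside the two-test group. Sample size and the primary analysis are unaffected.
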